## Abstract

**Background:**

Delay to start antiretroviral therapy (ART) and nonadherence compromise the health and wellbeing of people living with HIV (PLWH), raise the cost of care and increase risk of transmission to sexual partners. To date, interventions to improve adherence to ART have had limited success, perhaps because they have failed to systematically elicit and address both perceptual and practical barriers to adherence. The primary aim of this study is to determine the efficacy of the Supporting UPtake and Adherence (SUPA) intervention.

**Methods:**

This study comprises 2 phases. Phase 1 is an observational cohort study, in which PLWH who are ART naïve and recommended to take ART by their clinician complete a questionnaire assessing their beliefs about ART over 12 months. Phase 2 is a randomised controlled trial (RCT) nested within the observational cohort study to investigate the effectiveness of the SUPA intervention on adherence to ART. PLWH at risk of nonadherence (based on their beliefs about ART) will be recruited and randomised 1:1 to the intervention (SUPA intervention + usual care) and control (usual care) arms. The SUPA intervention involves 4 tailored treatment support sessions delivered by a Research Nurse utilising a collaborative Cognitive Behavioural Therapy (CBT) and Motivational Interviewing (MI) approach. Sessions are tailored to individual needs and preferences based on the individual patient’s perceptions and practical barriers to ART. An animation series and intervention manual have been developed to communicate a rationale for the personal necessity for ART and illustrate concerns and potential solutions. The primary outcome is adherence to ART measured using Medication Event Monitoring System (MEMS). Three hundred seventy-two patients will be sufficient to detect a 15% difference in adherence with 80% power and an alpha of 0.05. Costs will be compared between intervention and control groups. Costs will be combined with the primary outcome in cost-effectiveness analyses. Quality adjusted life-years (QALYs) will also be estimated over the follow-up period and used in the analyses.

**Discussion:**

The findings will enable patients, healthcare providers and policy makers to make informed decisions about the value of the SUPA intervention.

**Trial registration:**

The trial was retrospectively registered 21/02/2014, ISRCTN35514212.

**Electronic supplementary material:**

The online version of this article (10.1186/s12889-019-6893-z) contains supplementary material, which is available to authorized users.

## Background

Antiretroviral therapy (ART) has resulted in near-normal life expectancy for many people living with HIV (PLWH) [1] and there is solid evidence that viral suppression in PLWH taking ART prevents sexual transmission of HIV [2]. In the UK, uptake of ART among people with diagnosed HIV attending healthcare services is generally high, but a significant number of PLWH are not on ART [3]. The number of people with diagnosed HIV who are not taking ART is likely to be an underestimate because not everyone who is prescribed ART actually receives or takes it [4]. Furthermore, several studies show that nonadherence to ART remains suboptimal: a meta-analysis of 84 studies across 20 different countries found the mean rate of ART adherence (defined as ≥90%) was 62% [5]. In a more recent UK study, 873 (32%) of 2704 people taking ART reported nonadherence [6]. Delay to start ART and nonadherence compromise the health and wellbeing of individual patients, raise the cost of care and impact on public health through increased risk of transmission [7, 8]. Adherence to effective treatment should not only improve physical health, but also psychological wellbeing by empowering patients to take an active role in managing their condition [9]. Interventions to increase adherence to medicines have had limited success and it is not clear which strategies are most effective. Systematic reviews of adherence interventions have reported variable findings [10–13]. A recent recent comprehensive systematic review and meta-analysis of interventions to increase adherence to ART found that a variety of different types of interventions (e.g. interventions delivered via short message service (SMS), counselling and interventions delivered by a treatment supporter) were effective but effect sizes were generally small and the review did not specify specific intervention content or theoretical approaches that were effective [14].

In order to address this, we developed the Supporting Uptake and Adherence to ART (SUPA) intervention. In line with the guidance of the Medical Research Council (MRC) [15], the intervention was informed by our preparatory research in which we explored and developed relevant theory. In our preliminary studies, ART nonadherence had multiple causes for a given individual, both intentional and unintentional [16]. We subsequently identified the salient beliefs about medicines influencing adherence [16]. In studies across a range of illnesses and in different cultural contexts, adherence was consistently related to how patients judged their personal necessity for treatment relative to their concerns about potential adverse effects [17]. Studies conducted with PLWH demonstrated the utility of this Necessity Concerns Framework (NCF) for predicting ART uptake and adherence [18, 19].

In addition to perceptual factors influencing adherence, the National Institute for Clinical Excellence (NICE) recommends addressing practical factors such as limitations in capacity and resources: the Perceptions and Practicalities Approach (PAPA) [20]. To date, few interventions have utilised this approach. One exception is a telephone-based medicines support intervention, where patients receiving the intervention had fewer doubts about necessity and fewer concerns, fewer medication problems and higher reported adherence than standard care controls [21].

The content of the SUPA intervention has been described in detail ([name], [name], [name], [name], [name], [name], SUPA Group: The development of an intervention to support uptake and adherence to antiretroviral therapy in people living with HIV: the SUPA intervention, submitted). In summary, the SUPA intervention uses a Perceptions and Practicalities Approach (PAPA) to support uptake and adherence to ART. It comprises 3 key elements aiming to address factors related to the motivation to take treatment, elicit and help the patient overcome barriers to implementing the intention to take treatment and help them establish routines leading to habit formation:Communicate a common-sense rationale for ARTElicit and address specific Necessity beliefs and Concerns about ARTIdentify and address practical barriers to ART uptake and adherence.

This paper describes the protocol of a study to determine the efficacy of the SUPA intervention for increasing uptake and adherence to ART.

### Primary objective

To investigate the impact of the SUPA intervention on adherence to ART

### Secondary objectives

To investigate the impact of the SUPA intervention on treatment outcomes, engagement with care and patient-reported outcomesTo assess how patients’ beliefs about ART change over time and how this may predict adherence and engagement in careTo assess the costs and cost effectiveness of providing the intervention in the short and long-term.

## Methods

### Study design

This study comprises 2 phases (Fig. 1). Phase 1 is an observational cohort study, in which PLWH who are ART naïve and recommended to take ART by their clinician complete a questionnaire assessing their beliefs about ART over a period of 12 months. Phase 2 is a randomised controlled trial (RCT) nested within the observational cohort study to investigate the effectiveness of the SUPA intervention on adherence to ART and to explore the intervention mechanism. PLWH who are at risk of nonadherence will be recruited and randomised 1:1 to the intervention and control arms. All participants will receive usual care which is provided to all NHS patients through clinical support from a multi-disciplinary healthcare team including the patient’s assigned HIV physician, nurses, pharmacists and other healthcare professionals, such as clinical psychologists, as required. In addition, participants in the intervention arm will receive the SUPA intervention.

**Fig. 1 Fig1:**
[figure not shown]
Adapted CONSORT diagram of the study

### Setting

This study will be conducted in HIV clinics in National Health Service (NHS) hospitals across England: Kings College Hospital, Homerton University Hospital, Queen Elizabeth hospital (Woolwich), University Hospital Lewisham, North Middlesex University Hospital, St. George’s Hospital, University Hospitals Birmingham and Bradford Teaching Hospitals. The sites were selected on the basis of clinician-reported issues with suboptimal appointment attendance post HIV diagnosis.

### Participants

#### Inclusion and exclusion criteria

Participant inclusion criteria (Phases 1 and 2): (1) patients aged 18 years or above; (2) diagnosed HIV infection; (3) no previous prescription of ART (except women who have previously been prescribed ART for prevention of transmission during pregnancy and subsequently discontinued, who are considered eligible); (4) clinical recommendation to initiate ART treatment according to contemporaneous British HIV Association (BHIVA) guidelines or as deemed appropriate by the patient’s clinician; (5) able to provide written informed consent and available for long-term follow-up. Participant exclusion criteria: (1) patients who do not speak English; (2) those who plan to leave the country in the next 12 months and hence will not be available for follow-up appointments or telephone follow-ups; (3) participants already enrolled in a trial or in any research study which encourages adherence (e.g. clinical trial of an investigational medical product); (4) lack of capacity to provide informed consent; (5) hospitalisation for a mental disorder in the past 2 years; (6) current suicidality or self-harm; (7) pervasive developmental disorder; (8) active substance misuse/dependence in last 3 months which in the opinion of the physician or investigator renders the patient unable to adhere to the study protocol; (9) patients who have previously started antiretroviral therapy and subsequently discontinued, except if they have previously taken ART for pregnancy; (10) psychiatric or addictive disorders which in the opinion of the clinician or investigator could preclude obtaining informed consent.

### Recruitment

A two-stage enrolment process will be employed: Patients who meet the inclusion criteria will be informed about the study by their HIV doctor, and will subsequently be referred to the study team. All patients who meet the inclusion criteria will be invited to participate in the observational component of the study (Phase 1). Following informed consent, all participants will complete the Beliefs about Medicines Questionnaire-ART specific version (BMQ-ART). The clinician or Research Assistant (RA) will score the questionnaire immediately. If the score indicates that the participant is at high risk for nonadherence (ART-Necessity score ≤ 3 and/or ART-Concerns score ≥ 3), they will be provided with information by the study team and invited to consider taking part in Phase 2, the interventional trial component. Further written informed consent to take part in Phase 2 will be received after the patient has been given an opportunity to consider their participation in the study and discuss this with others if they wish.

### Confidentiality

The study will conform to the Caldicott Principles and ethical and legal guidelines covering consent, confidentiality and storage of data. All data will be kept confidential in accordance with the Data Protection Act. All participants will be allocated a study identification number, so the participants will only be identifiable to study staff. De-identified data (no name, date of birth) will be stored in a password-protected database at the UCL School of Pharmacy for 15 years. After that time the study register, Case Report Forms (CRFs), and consent forms will be destroyed making it impossible to link participants’ names to identification numbers. The original copy of the consent form will be stored in the patient’s case notes and a copy of the consent form will be kept in the site file.

### Randomisation

If the participant consents to participate in Phase 2, they will be randomly allocated to one of the two trial arms (open randomisation; ratio 1:1) by the King’s Clinical Trials Unit (KCTU), King’s College London. The randomisation procedure will be a stratified block randomisation. Centres will be blocked to ensure that there are equal participants in each arm at each site. The randomisation schedule will be incorporated into a dedicated electronic database and kept securely within this electronic system, inaccessible to the enrolment location. Once an eligible participant has given written informed consent and completed the baseline assessment, the RA will log on to the randomisation system, enter the participant identification number and hospital, and will click on the ‘randomise’ function. The treatment allocation will appear immediately on screen and be communicated to the patient. The confirmation of treatment allocation details will be sent to the research team immediately. The RA will inform the participant’s HIV clinical team on the same day. Movement from the observational cohort to the intervention trial or declining participation in the trial will be recorded on the central database.

### Control: care as usual (CAU)

All participants (intervention and control group) will receive care as usual. Although this may vary slightly by clinic, this follows the same framework across all sites.If the participant is starting ART, standard of care typically includes:Discussion with a doctor about starting ART (including why, what is involved and the importance of adherence);Consultation with a pharmacist at first prescription discussing the importance of adherence and potential side effects;Collection of 2–4 weeks of medication and appointment with clinic nurse for safety bloods at 2–4 weeks;Review with their HIV doctor at 1 month;Routine clinic visits at 3 or 6 monthly intervals with a nurse and HIV doctor.If the participant is not starting ART:3 monthly consultation with HIV doctor, discussing readiness and beliefs about medication with a view to commencing ART;3 monthly monitoring bloods with nurse.

### Intervention: SUPA intervention + care as usual (CAU)

The SUPA intervention has been described in detail in a separate publication ([name], [name], [name], [name], [name], [name]: SUPA Group. The development of an intervention to support uptake and adherence to antiretroviral therapy in people living with HIV: the SUPA intervention, submitted). Patients randomised to the intervention group will receive treatment initiation support within 1 month of enrolment into the intervention trial. This support will be in the form of 4 tailored treatment support sessions delivered by a Research Nurse (RN) utilising a collaborative Cognitive Behavioural Therapy (CBT) and Motivational Interviewing (MI) approach. The sessions will be conducted face-to-face (or by telephone if the patient prefers or cannot meet face to face) and will communicate a rationale for the personal necessity of medication, elicit and address concerns about medication and problem-solve potential practical barriers to adherence. Sessions will be tailored to individual needs and preferences, based on (1) the individual patient’s perceptions and practical barriers to ART identified using the BMQ-ART, and (2) salient issues arising during the sessions. An animation series and intervention manual have been developed as tools to communicate a rationale for the personal necessity of ART and to illustrate concerns and potential solutions. The specific timing of the sessions will differ according to the patient’s specific needs and availability; however, the first two sessions will take place within 1 month of enrolment, and sessions 3 and 4 will provide additional support 3 and 6 months post randomisation. These appointments will be scheduled at the patient’s convenience.

### Assessment of intervention fidelity

If the patient consents to audio recording, the intervention sessions will be recorded on a dictaphone. As in previous intervention trials [22], a scale will be developed to rate the recorded sessions according to a rating protocol. Two trained raters working independently will score randomly selected intervention recordings (1 intervention session from 20% of participants). Differences in ratings will be identified, discussed and resolved through a process of consensus and conciliation.

### Participants who delay starting ART (both arms)

If participants delay or decline ART when treatment is offered by their clinician, they will continue in the study. For the intervention group, sessions will focus on barriers to starting treatment, rather than ongoing support with adherence.

### Participant follow-up

#### Phase 1 - observational cohort study

At baseline and at the participant’s routine clinic visits 3, 6, and 12 months post-baseline, the participant will complete the observational study questionnaires (Additional file 1). If the participant does not have 3-monthly appointments as standard care, or are not attending clinical appointments, they will be asked to either schedule a research visit or complete the questionnaires over the phone with a member of the research team.

#### Phase 2 – randomised controlled trial

For trial participants, the baseline visit includes enrolment, randomisation and completion of the trial study questionnaires (Additional file 2). For intervention participants, this includes their first intervention session. Participants in the intervention arm will then be invited to attend additional study visits at 1, 3, 6 and 12-months post-randomisation. Participants in the control arm will be invited to attend additional study visits at 3, 6 and 12 months post-randomisation (Fig. 1). Expenses for study visits will bereimbursed (£10 per visit).

### Data collection

#### Medication event monitoring system (MEMS)

When a participant chooses to initiate treatment, the pharmacy in each site will dispense the participant’s prescription in bottles approved by the SUPA study for use with a Medication Event Monitoring System (MEMS) TrackCap. Site pharmacists will receive training by a designated RA in the use of MEMS caps, and how to explain the use of MEMS cap to participants. The RA will also explain to the participant how to use the MEMS bottle and cap. If the first dispensing of ART in a MEMS bottle does not coincide with a research visit, the RA will contact the participant via telephone to give any necessary further explanation on how to use the MEMS cap. Participants will be offered an instruction sheet which will be given at their research visit. All pharmacy refill data available for each participant from starting treatment up to an including their most recent clinic visit will be collected electronically.

Self-report measures will be completed by the participant with the help of the RA (if desired) at each study visit. All medical data will be collected by the RA from available patient notes and lab results. Baseline data will be collected at the enrolment visit. Measures completed at each assessment are shown in Additional files 1 and 2.

### Primary endpoint

#### The proportion of months under follow-up where adherence is greater than or equal to 90%

Adherence is defined by MEMS data. As the distribution of this variable is unknown, we will categorise the proportion of participants achieving ≥90% adherence as < vs ≥0.8 of the follow-up months. Essentially, this study assesses whether the participant has been ≥90% adherent for at least 80% of their time spent in the trial. The 80% threshold to define a good outcome is based on the fact that 4–6 weeks delay to ART initiation following a treatment recommendation is reasonable, and if followed by consistent ≥90% adherence to ART for the remainder of the trial (10 of the 12 months), the participant is likely to achieve and maintain viral load suppression. To calculate each monthly adherence value, the percentage of adherence (according to MEMS) for each individual over each month of follow-up from randomisation will be calculated, treating every day off ART or not taking all prescribed ART doses (indicating either nonadherence or delayed treatment initiation) as 0% adherence.

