### Statistical methods and analysis

The SUPA intervention is hypothesised to be superior to care as usual, and therefore the planned analysis is intention to treat, including all randomised participants, with all participants analysed according to the study group to which they were randomised regardless of subsequent treatment received. Primary analysis will include all randomised participants other than those randomised in error (defined as not intending to randomise the participant through e.g. miscommunication, rather than a participant or clinician decision once the allocation has been given).

A per-protocol analysis will be carried out on the primary endpoint including all participants in the intervention group who attended all 4 (2 + 1 + 1) sessions. If the intention to treat and per-protocol analyses on the primary endpoint leads to inconsistent results, then per-protocol analysis will also be carried out on all the other endpoints.

Continuous variables will be summarised by medians and IQRs or means and standard deviations as appropriate depending on the distribution, and compared between groups using ranksum tests or t-tests respectively. Comparisons of change from baseline in continuous variables will adjust for any baseline imbalances using either quantile or normal linear regression (depending on the shape of the distribution).

Categorical variables will be summarised by frequency tables, and compared between groups using chi-squared tests, unless any cell count is < 5 or cell percentage is < 5% in which case exact tests will be used. Binary variables will be summarised by percentages, using standard exact 95% CI for the risk differences. Time-to-event variables will be summarised using Kaplan-Meier curves and average differences between randomised groups estimated using Cox models. Patients without the event recorded will be censored at their last clinic visit. Proportionality of hazards will be tested; where significant departures exist, varying differences between randomised groups over time will be estimated using flexible parametric models of Royston and Parmar. Rate of treatment switching will be analysed using Poisson regression, including all changes to ART as events and the total time under follow-up through the earliest of 12 months or the last patient visit as the person-time at risk. Primary analysis will not stratify by clinical centre.

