### Trial discontinuation

If a member of the clinical care team or the RN feels that the intervention is detrimental (for example, causing distress), the patient can be referred out of the intervention. Referral to a more specialised professional should be carried out by the patient’s Clinician. Participants may discontinue from participation at any time, at the discretion of the Investigator. Specific reasons for discontinuing a participant from either study are:Withdrawal of informed consent.Development of exclusion criteria or other safety reasons during the study.Incorrect enrolment or randomisation of the participant.

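### The primary endpoint is scored over each participant's own time in the trial, but its 0.8 cut is justified only for a full 12 months, so withdrawal or short follow-up can misclassify success and failure

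*Protocol article*

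**What the plan says.** All of this is in the Protocol article.

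- **Endpoint variable.** The heading under Primary endpoint gives it as "The proportion of months under follow-up where adherence is greater than or equal to 90" per cent.
- **Cut.** The text below that heading says "we will categorise the proportion of participants achieving ≥90% adherence as < vs ≥0.8 of the follow-up months". It then restates the question in plain words as "whether the participant has been ≥90% adherent for at least 80% of their time spent in the trial".
- **Rationale for the cut.** It rests on two statements: that "4–6 weeks delay to ART initiation following a treatment recommendation is reasonable", and that adherence of 90% or more then continues "for the remainder of the trial (10 of the 12 months".
- **Monthly score.** Adherence is computed from MEMS for each follow-up month counted from randomisation. Days off ART, or with doses missed, score 0%. The reasons named for a zero are nonadherence and delayed initiation; leaving the trial is not named.
- **Who is analysed.** Under Statistical methods and analysis, "the planned analysis is intention to treat, including all randomised participants", with only those randomised in error left out.
- **Early exit is foreseen.** Trial discontinuation lists reasons for ending participation. Strategies to promote data completeness provides for full withdrawal, with earlier data kept if the participant agrees.

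**The concern.** The endpoint's definition and its justification use different denominators. The definition uses the participant's own follow-up, and the justification uses 12 months. They agree only for someone followed for the full year.

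For anyone with shorter follow-up, the same 0.8 cut tolerates a different number of poor months, and the start-up delay that the protocol calls reasonable can be enough for failure. In the other direction, a short clean record followed by withdrawal counts as success, although nothing is known about the later months. Because all randomised participants are analysed, these people have to be classified one way or the other.

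What is at stake is who counts as a primary success. The arms have different contact schedules (Intervention and Participant follow-up sections), so it is plausible, though not shown, that length of follow-up differs between them.

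**Working it through.** **1. The plan's own figure.** Inputs from Sample size calculations, Phase 2: 45% versus 60%, two-sided alpha 0.05, 80% power. The two-proportion formula without continuity correction gives 173 per arm. With the correction, n = (n₀/4)·[1 + √(1 + 4/(n₀d))]², where n₀ is the uncorrected size (172.8 before rounding) and d = 0.15, it gives 186 per arm, or 372 in total. The corrected formula reproduces all five rows of Table 1 (183, 186, 183, 165, 134), so it is the one used for power below.

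**2. What the cut means at each length of follow-up.** Months needed = 0.8k rounded up, for k months of follow-up.

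| k | Months needed | Months below 90% allowed |
|---|---|---|
| 1–4 | all k | 0 |
| 5–9 | k − 1 | 1 |
| 10–12 | k − 2 | 2 |

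- Two clean months, then withdrawal: 2/2 = 1.0, success. Over 12 months with later months scored as not adherent: 2/12 = 0.17, failure.
- Two-month delay, then perfect adherence, follow-up ending at month 9: 7/9 = 0.78, failure. A two-month delay passes only if (k − 2)/k ≥ 0.8, that is k ≥ 10.
- One-month delay, then perfect adherence: failure for k ≤ 4, success from k = 5.

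To show that the cut shifts even when behaviour does not, assume an independent 80% chance that any month is adherent. The probability of success is then 0.80 at k = 1, 0.41 at k = 4, 0.74 at k = 5, 0.44 at k = 9, 0.68 at k = 10 and 0.56 at k = 12. It is not even monotone in k.

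**3. Possible effect on the comparison.** The documents give no dropout rate, so these inputs are assumptions: 45% success among completers in both arms (no effect), loss L before month 10 of 20% in one arm and 10% in the other, and a share g of leavers who meet the cut on their own time.

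- Own-time rule: success = (1 − L)·0.45 + L·g.
- Fixed 12-month rule, loss scored as failure: success = (1 − L)·0.45.

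| g | Own-time rule: 20% loss vs 10% loss | Difference | Fixed rule: 36.0% vs 40.5% | Shift between rules |
|---|---|---|---|---|
| 0.5 | 46.0% vs 45.5% | +0.5 | −4.5 | 5.0 points |
| 0.6 | 48.0% vs 46.5% | +1.5 | −4.5 | 6.0 points |
| 0.8 | 52.0% vs 48.5% | +3.5 | −4.5 | 8.0 points |

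Differences are for the arm that loses more. The shift is (0.20 − 0.10)·g.

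**4. Power if loss is scored as failure.** With 186 per arm, both percentages are multiplied by (1 − loss), using the continuity-corrected formula.

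| Assumed loss | Percentages | Difference | Power |
|---|---|---|---|
| 0% | 45.0 vs 60.0 | 15.0 | 80% |
| 10% | 40.5 vs 54.0 | 13.5 | 71% |
| 15% | 38.25 vs 51.0 | 12.75 | 66% |

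**5. A related wording slip.** Table 1 heads its columns with more than 0.8, while the text uses 0.8 or more. The two differ only where 0.8k is a whole number: 4/5 at k = 5 and 8/10 at k = 10. At k = 12 the cut is 9.6 months and they cannot differ.

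**The case against.** The strongest reply is that the documents do not say that follow-up for this endpoint ends when a participant stops attending. Days off ART score 0%, people who delay or decline ART stay in the study, telephone follow-up is offered, and MEMS caps are sought even from those who withdraw. The rule that ends time at the last visit is stated only for the switching-rate analysis. This stands: someone who stops attending without withdrawing may be read as still under follow-up and accruing 0% months. The problem is therefore clearest for withdrawal or otherwise truncated follow-up. A separate analysis plan may also set rules for missing MEMS data. But the denominator is stated in the article, so it is not merely a detail left for later.

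Three stronger readings are tempting and are not supported:

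- **Stopping ART produces a perfect record.** A reader might combine the discontinuation reason "Development of exclusion criteria or other safety reasons during the study" with the exclusion of "patients who have previously started antiretroviral therapy and subsequently discontinued, except if they have previously taken ART for pregnancy" and infer that someone who stops ART leaves with a clean score. Days off ART are themselves scored 0%, and four of them bring a 30-day month to 26/30 = 87%. In the first four months one such month is already failure. The exclusion is also worded as an entry criterion, and the discontinuation section does not say that outcome data collection stops.
- **Intention to treat is contradicted.** Everyone randomised is still analysed in the allocated arm. This is a fault in the endpoint definition, not in the analysis population.
- **The rule creates a spurious 5-point difference.** With half of leavers clean, the observed difference is 0.5 points. Five points is the distance from the fixed rule, which itself shows −4.5 with no effect among completers.

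**Conclusion.** The point holds for participants with less than 12 months of follow-up. As written, the rule can count a brief clean record before withdrawal as success, and can count the protocol's own reasonable delay as failure when follow-up ends before month 10. Both results follow from the stated text by arithmetic and need no assumption about dropout.

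The effect on the trial result does depend on assumptions. Its direction turns on who leaves, when and from which arm. Under loss of 20% versus 10%, 45% success among completers in both arms and 50–80% of leavers clean, the own-time rule shows about +0.5 to +3.5 points for the arm that loses more, and the fixed rule with loss as failure shows −4.5. Neither figure is the true effect. What they show is that an unsettled choice of rule can move the between-arm difference by 5–8 points against a 15-point target, which is enough to require settling it before the data are seen.

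**What to change.** 1. Define success as at least 10 of the 12 months from randomisation with adherence of 90% or more, for every randomised participant.
2. State one primary scoring rule for months after withdrawal or loss. For example, score them below 90% unless the pharmacy refill data already being collected show ART continuing. Use multiple imputation of those months as a sensitivity analysis only, so that the same months are not both scored and imputed in the primary analysis.
3. State that discontinuation under Trial discontinuation does not, as far as consent allows, end outcome data collection, and does not remove a participant from the analysis described under Statistical methods and analysis.
4. Align Table 1 with the text on 0.8 or more.

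The cost is wording in the protocol and analysis plan. No new data are needed, and Trial status reports that no cleaning or analysis had been done when the article was submitted. The downside is that, if loss is scored as failure, the stated 80% power should be restated: about 71% with 10% loss and 66% with 15% loss at 186 per arm and 45% versus 60% (assumed rates). Scoring loss as failure will also misclassify people who leave while still taking ART elsewhere, which is why the refill data and the sensitivity analysis are needed.
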